### Statistical analyses

We plan to enroll 80 patients in each group. Comparison between EES and BES with BVS will necessitate a total of 240 patients in order to achieve a power of 90% to prove a difference of 0.2 mm LLL at 9 months (BES and EES = 0.3 mm vs BVS 0.5 mm; SD 0.5 mm). This allows for a dropout rate of 20% of the sample in which case the study would still yield a power of 83%. Sample size calculations were performed using Sample Power 3 (SPSS Inc, Chicago, IL, USA) at a two-tailed significance level of α = 0.05.

Continuous variables are presented as mean ± standard deviation or median (25% to 75%) interquartile range according to their distribution. Categorical variables are presented as counts and percentages. Comparison between the individual groups and comparison between BES and EES and BVS are performed on demographical data and risk factors as well as on procedural characteristics. The primary outcome is analyzed using a parametric or nonparametric test according to distribution and by the computation of a multivariate linear analysis by taking into account significant risk factors that potentially influence outcome thus adjusting for them. Clinical endpoints are compared using the Kaplan-Meier method. Binary logistic regression is equally performed in the search of independent predictors for the secondary endpoints. All analyses are performed according to the intention-to-treat principle. An intermediate analysis will be performed after follow-up angiography of 40 patients in each group.

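### The stated 90% power (83% after 20% dropout) does not follow from the stated two-tailed 0.05 test, which gives 83% and 74%; a one-tailed test reproduces both printed figures

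*Protocol article*

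**What the plan says.** All the planning figures stand in the first paragraph of the Statistical analyses section of the protocol article.

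- Group size: "We plan to enroll 80 patients in each group", for three groups.
- Contrast: "Comparison between EES and BES with BVS".
- Target: "to prove a difference of 0.2 mm LLL at 9 months", with the assumptions "BES and EES = 0.3 mm vs BVS 0.5 mm; SD 0.5 mm".
- Power at full enrolment: the comparison "will necessitate a total of 240 patients in order to achieve a power of 90" per cent.
- Power after losses: "This allows for a dropout rate of 20% of the sample in which case the study would still yield a power of 83" per cent.
- Test: "at a two-tailed significance level of α = 0.05".

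The Study endpoints section names late lumen loss (LLL) at 9 months as the only primary endpoint. This paragraph is the only justification of the sample size in the article.

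**The concern.** The paragraph prints every input that a two-sample power calculation needs, together with the result, so the result can be checked directly. At two-tailed 0.05 neither power figure comes out. Both come out almost exactly if the test is one-tailed.

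At stake is how a null result on the primary endpoint would be read. The endpoint needs a repeat invasive angiogram at 9 months, and the plan itself allows for 20% loss. At that loss the printed figure implies a type II error of 17% (100 − 83), whereas the printed inputs imply about 26% (100 − 74). A reader relying on the printed figures would take a non-significant LLL comparison as stronger evidence against a 0.2 mm difference than the design can supply.

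**Working it through.** **Inputs (protocol article, Statistical analyses).** Difference δ = 0.5 − 0.3 = 0.2 mm; SD σ = 0.5 mm; α = 0.05, two-tailed; 80 per group. The contrast is read as BVS (n₁ = 80) against EES and BES pooled (n₂ = 160). After 20% loss spread evenly, n₁ = 64 and n₂ = 128, total 192.

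**Formula.** SE = σ√(1/n₁ + 1/n₂) and λ = δ/SE. In the normal approximation, power ≈ Φ(λ − z), with z = 1.960 two-tailed or 1.645 one-tailed. The exact value uses the noncentral t with n₁ + n₂ − 2 degrees of freedom and noncentrality λ.

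**Full enrolment, 80 against 160.**
- SE = 0.5 × √(1/80 + 1/160) = 0.0685, so λ = 0.2/0.0685 = 2.921.
- Two-tailed: Φ(2.921 − 1.960) = Φ(0.961) = 83.2%.
- One-tailed: Φ(2.921 − 1.645) = Φ(1.276) = 89.9%.

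**After 20% loss, 64 against 128.**
- SE = 0.5 × √(1/64 + 1/128) = 0.0765, so λ = 0.2/0.0765 = 2.613.
- Two-tailed: Φ(2.613 − 1.960) = Φ(0.653) = 74.3%.
- One-tailed: Φ(2.613 − 1.645) = Φ(0.968) = 83.3%.

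**Against the plan's figures (noncentral t).**

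| | Plan | Two-tailed 0.05 | One-tailed 0.05 |
|---|---|---|---|
| 80 vs 160 | 90% | 82.9% | 89.8% |
| 64 vs 128 | 83% | 73.9% | 83.1% |

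The one-tailed column reproduces both printed values; the two-tailed column misses by about 7 and 9 points.

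**Other readings of the comparison, all at two-tailed 0.05.**

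| Reading | Full enrolment | After 20% loss |
|---|---|---|
| BVS against one other stent (80 vs 80; 64 vs 64) | 71.0% | 61.2% |
| Three-group F-test (80 or 64 per group) | 74.1% | 63.6% |
| Even split, not the design (120 vs 120; 96 vs 96) | 87.0% | 78.7% |

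None reaches 90% and 83%. Of the contrasts that three groups of 80 allow, the pooled one is the most favourable.

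**What 90% would take at two-tailed 0.05.**
- Sample size: n₁ = (1.960 + 1.282)² × 0.5² × (1 + 1/2)/0.2² = 98.5. The normal approximation thus needs 99 against 198 (297 patients). By the noncentral t that gives 89.96%, so 100 against 200 (300 evaluable patients, power 90.2%) is needed.
- Detectable difference: (1.960 + 1.282) × SE = 3.242 × 0.0685 = 0.22 mm with 240 evaluable patients, and 3.242 × 0.0765 = 0.25 mm with 192.

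**The case against.** The strongest reply accepts the arithmetic and disputes the cause and the remedy. The text says two-tailed outright, and changing another single input gives much the same pair at two-tailed 0.05:

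- an SD of 0.45 mm: 89.8% and 82.3%;
- a difference of 0.225 mm: 90.5% and 83.3%;
- 300 patients falling to 240: 90.2% and 82.9%.

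The means and SD are printed to one decimal, so the first two could be rounding in the report. If so, restating the power would correct the wrong number. This stands as a limit on the diagnosis: the one-tailed run is an inference. It does not rescue the paragraph, because under each explanation at least one printed number is wrong.

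A second point is that the article never says in so many words that EES and BES are pooled, and its null hypothesis concerns all three stents. That is fair, and the corrected figures should be tied to the pooled contrast. It does not help the printed figures, since the pairwise and three-group readings give lower power still.

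Third, the planned covariate-adjusted model might be more powerful than an unadjusted comparison. The article quantifies no such gain, and its printed calculation includes none.

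Last, recruitment is complete, type I error is untouched, and a confidence interval will show the precision achieved. All true. This makes the correction cheap, but the planning claim remains wrong as printed.

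**Conclusion.** The concern holds. On the printed inputs, power for BVS against pooled EES and BES at two-tailed 0.05 is 83% with all 240 patients evaluable and 74% with 192, not 90% and 83%.

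The corrected figures assume the pooled 1:2 contrast, a common SD of 0.5 mm, a true difference of 0.2 mm, losses spread evenly over the groups and an unadjusted two-sample comparison. They do not depend on how the error arose. A one-tailed calculation is the most likely source, because it matches both figures to about 0.2 points with no other input changed, but the document does not prove it.

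**What to change.** Keep the two-tailed test and the 240 patients. In the Statistical analyses section, replace the two power figures with wording such as: *for BVS (80) against EES and BES pooled (160), a difference of 0.2 mm with SD 0.5 mm is detected with 83% power at two-tailed α = 0.05 if all 240 patients are evaluable, and with 74% power if 20% lack the 9-month angiogram; the differences detectable with 90% power are about 0.22 mm and 0.25 mm respectively.*

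First check the saved sample-size run. If it used another SD, difference or sample size, print the input actually used and the power that follows from it. Changing the declared test to one-tailed to preserve the 90% is not a remedy: the stated hypothesis is one of difference between the stents, without a direction.

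The cost is wording and a less favourable power statement. No patients are added; the Trial status section reports recruitment complete, so the sample size can no longer be raised in any case.

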### Study endpoints

The primary endpoint is LLL at 9 months as assessed by quantitative coronary angiography. The secondary endpoints are divided in angiographic and clinical findings. We will assess angiographic success, device success and binary restenosis at 9 months. Clinical endpoints include a patient-oriented MACE (composite of death, MI and TVR) a device-oriented MACE (composite of cardiac death, MI and target lesion revascularization (TLR)) and stent thrombosis (ST) at 6 months, and 1, 2 and 5 years.

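### Late lumen loss gets two analyses, both shaped by the data, and the plan does not say which one decides the trial

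*Protocol article*

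**What the plan says.** The Study endpoints section fixes the endpoint: "The primary endpoint is LLL at 9 months as assessed by quantitative coronary angiography". The section on follow-up angiography defines it as in-segment loss.

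The Statistical analyses section then gives the analysis in a single sentence with two halves joined by a plain conjunction. The first half: "The primary outcome is analyzed using a parametric or nonparametric test according to distribution". The second half: "by the computation of a multivariate linear analysis by taking into account significant risk factors that potentially influence outcome thus adjusting for them". The article gives no rule for judging the distribution, no list of risk factors and no criterion for significance, and it does not order the two results.

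The preceding sentence plans between-group comparisons: "Comparison between the individual groups and comparison between BES and EES and BVS are performed on demographical data and risk factors", extended to procedural characteristics. The sample size rests on a difference in means ("BES and EES = 0.3 mm vs BVS 0.5 mm; SD 0.5 mm"), "at a two-tailed significance level of α = 0.05".

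**The concern.** A confirmatory trial needs one result that answers its primary question. Here there are two, and each takes its final form from the data.

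- **No deciding result.** If the chosen test gives p = 0.03 and the adjusted model p = 0.07 (invented values), the document does not say which stands. That leaves room to claim success on whichever is favourable, and the chance of a false positive then exceeds 5%.
- **The target can change.** The trial is sized on a mean difference of 0.2 mm. A rank test addresses a different hypothesis and gives no estimate of that difference. The shape of the observed data would settle whether the sized hypothesis is tested at all.
- **The adjustment is undefined.** Significant could mean associated with LLL. Because the groups are also compared on risk factors, it could equally mean imbalanced between groups. The two readings lead to different models with different power.

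**Working it through.** **Inputs from the article (Statistical analyses):** 80 patients per arm; means 0.3 mm (BES and EES) and 0.5 mm (BVS), so δ = 0.2 mm; SD σ = 0.5 mm; two-sided α = 0.05; 20% dropout. The contrast of BVS with the two other stents pooled is 80 vs 160, or 64 vs 128 after dropout.

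**Assumed, because the article gives no figure:** R², the share of LLL variance explained by covariates, 0 to 0.3; ten candidate covariates, four of them prognostic (eight candidates in a second setting); entry at p < 0.05.

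**Step 1. The plan's own power.** Power = Φ(δ / [σ√(1/n₁ + 1/n₂)] − z).

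- 80 vs 160: 0.2 / (0.5 × √0.01875) = 2.921. Two-sided: Φ(2.921 − 1.960) = 83.2%.
- 64 vs 128: 0.2 / (0.5 × √0.02344) = 2.613. Two-sided: Φ(2.613 − 1.960) = 74.3%.

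The article states 90% and 83%. Those values appear only with a one-sided 0.05 level (z = 1.645), which gives 89.9% and 83.3%. That discrepancy is a separate matter. It is relevant here only because 83.2% and 74.3% are the right starting points for judging what adjustment adds.

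**Step 2. Type I error with no true difference.** Simulation of 80 vs 160, 6,000 trials per row, ten candidates. The test is chosen by a Shapiro–Wilk check, and covariates enter if associated with LLL at p < 0.05. The Monte Carlo standard error at 5% is √(0.05 × 0.95 / 6000), about 0.3 points.

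| R² | Errors | Chosen test | Selected-covariate model | Either one | Fixed model |
|---|---|---|---|---|---|
| 0 | normal | 5.00% | 4.93% | 5.38% | 4.98% |
| 0 | skewed | 4.92% | 5.15% | 6.73% | 5.12% |
| 0.1 | normal | 4.90% | 4.70% | 6.30% | 4.73% |
| 0.1 | skewed | 4.95% | 5.28% | 7.43% | 5.22% |
| 0.2 | normal | 4.98% | 4.80% | 6.97% | 4.85% |
| 0.2 | skewed | 5.13% | 4.73% | 7.65% | 4.80% |
| 0.3 | normal | 5.13% | 4.95% | 7.90% | 4.82% |
| 0.3 | skewed | 5.07% | 4.68% | 7.85% | 4.70% |

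With 64 vs 128, skewed LLL and eight candidates, the either-one rate is about 6.6% to 8.6%. Across both settings the range is 5.4% to 8.6%. If covariates are instead picked by baseline imbalance, the adjusted model alone is slightly conservative (4.1% to 4.5%).

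**Step 3. What a fixed adjusted model adds over no adjustment.** Replace σ by σ√(1 − R²), two-sided 0.05.

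| R² | 80 vs 160 | 64 vs 128 |
|---|---|---|
| 0 | 83.2% | 74.3% |
| 0.1 | Φ(3.079 − 1.960) = 86.8% | Φ(2.754 − 1.960) = 78.6% |
| 0.2 | Φ(3.266 − 1.960) = 90.4% | Φ(2.921 − 1.960) = 83.2% |

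**Step 4. What it adds over the readings of the adjustment rule.** Simulated power, 80 vs 160, 4,000 trials per row, normal errors.

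| R² | Unadjusted t test | Selected by imbalance | Selected by outcome, p < 0.05 | Fixed, four covariates |
|---|---|---|---|---|
| 0.1 | 83.4% | 83.4% | 85.3% | 86.3% |
| 0.2 | 83.2% | 83.3% | 90.0% | 90.5% |
| 0.3 | 83.6% | 84.6% | 93.4% | 93.4% |

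The fixed model beats outcome-based selection by about 1 point or less. It beats imbalance-based selection, or no adjustment, by roughly 3 to 10 points.

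**The case against.** The strongest reply has four parts.

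1. **Neither data-driven choice inflates error by itself.** This is correct. A reader might infer that choosing the test or the covariates from the data pushes type I error above 5%. Step 2 shows each analysis alone near 5%. The excess arises only if either result may be claimed, and the article does not state such a rule. It states no rule at all, so the excess is a risk left open, not a planned procedure.

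2. **The data analysts are blinded.** The Treatment assignment section says so, and both the distribution check and outcome-based selection can be done without knowing the arm. That limits deliberate picking, but it does not settle which of two finished results counts.

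3. **These are details for an analysis plan.** A covariate list, an entry threshold and a normality rule can fairly be left to one, and their absence is not the point. The article does fix a data-driven rule and sets two analyses of the primary outcome side by side. The unadjusted sample-size calculation might suggest that the linear model is only supportive, but the text does not say so.

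4. **The plan already adjusts, so little precision is lost.** This holds if outcome-selected covariates are used and that model decides. It does not hold if the unadjusted test decides or selection is by imbalance, and the article leaves all of these open.

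Two further inferences are tempting and unsupported. A reader might count three p-values (t test, rank test, adjusted model), but the text calls for one test or the other plus the model, which makes two. A reader might also infer adjustment for procedural variables, some of which could be effects of the device. The article says only that group comparisons "are performed on demographical data and risk factors as well as on procedural characteristics"; the adjustment sentence names risk factors, a category listed separately.

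**Conclusion.** The point holds in a limited form. The primary endpoint has two analyses with none named as deciding, and one branch would not test the mean difference on which the trial is sized. The type I error at stake is about 5.4% to 8.6% against a nominal 5%, conditional on success being claimable on either result. It rests on an assumed R² of 0 to 0.3, an assumed eight to ten candidate covariates and a 0.05 entry threshold. That is moderate, and it comes from the missing designation, not from either analysis alone.

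The precision gain depends on the comparison: 3 to 9 points of power against an unadjusted test at R² of 0.1 to 0.2, and about 1 point or less against outcome-selected covariates. The article gives no R², so these are illustrations and not forecasts. The change is worth making because it settles what the trial will conclude and costs almost nothing.

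**What to change.** Name one primary analysis: a linear model of in-segment LLL at 9 months on treatment, with a short list of covariates fixed by name before unblinding. Candidates are diabetes, acute coronary syndrome at presentation and reference vessel diameter. Presentation and vessel diameter bear on eligibility, and medical history is taken at baseline in Table 1. Report the mean difference in mm with its 95% CI, so that the result answers the 0.2 mm question.

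Make the unadjusted comparison and the rank test sensitivity analyses, and remove significance as the criterion for entering covariates. As a safeguard, state that only variables known before randomisation may enter the primary model.

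The cost is a few sentences in the protocol or analysis plan before unblinding. No extra patients, visits or measurements are needed.

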**Methods/Design:**

The EVERBIO II trial is a single-center, assessor-blinded, randomized trial. The study population consists of all patients aged ≥18 years old undergoing percutaneous coronary intervention. Exclusion criterion is where the lesion cannot be treated with BVS (reference vessel diameter >4.0 mm). A total of 240 patients will be enrolled and randomly assigned into 3 groups of 80 with either BVS, EES or BES implantation. All patients will undergo a follow-up angiography study at 9 months. Clinical follow-up for up to 5 years will be conducted by telephone. The primary endpoint is in-segment late lumen loss at 9 months measured by quantitative coronary angiography. Secondary endpoints are patient-oriented major adverse cardiac event (MACE) (death, myocardial infarction and target-vessel revascularization), device-oriented MACE (cardiac death, myocardial infarction and target-lesion revascularization), stent thrombosis according to ARC and binary restenosis at follow-up 12 months angiography.

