The unresolved problem of neointimal proliferation and very late stent thrombosis from lingering polymers and vascular scaffolds, led to the development of new-generation completely resorbable stents. The Absorb™ (Abbott Vascular, Abbott Park, IL, USA) is the first CE approved DES with a bioresorbable vascular scaffold (BVS). It uses a poly-l-lactide polymer that is absorbed after approximately 2 years via the Krebs cycle. A prospective, open-label, 2-stage study called ABSORB including 131 patients was conducted in Europe and New Zealand and led to its approval by the EU in January 2011 for the treatment of coronary artery lesions [14]. The major adverse cardiac event (MACE) rate was reported as 6.8% at 2-years follow-up and late lumen loss (LLL) 0.27 mm at 12 months [15,16]. Its non-inferiority to the Xience Prime (Abbott Vascular), an EES, is currently under investigation in the international ABSORB EXTEND trial that plans to enroll 1,000 patients (NCT01023789). To date, there is no data on BVS compared to EES or BES, and independent trials are eagerly awaited. We seek to compare the efficacy and safety profiles of these three different types and generations of DES.

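### Kaplan-Meier is named for all clinical endpoints, but device-oriented MACE and stent thrombosis leave some deaths outside the endpoint, so 5-year risks read from 1 − KM would be slightly too high

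*Protocol article*

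**What the plan says.** The Statistical analyses section of the protocol article states: "Clinical endpoints are compared using the Kaplan-Meier method". It exempts no endpoint, names no accompanying test, and does not say how a death outside an endpoint is handled.

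The Study endpoints section defines the clinical endpoints:

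- "a patient-oriented MACE (composite of death, MI and TVR"), in which every death is an event;
- "a device-oriented MACE (composite of cardiac death, MI and target lesion revascularization (TLR")), in which only cardiac death is an event;
- "stent thrombosis (ST) at 6 months, and 1, 2 and 5 years", listed as an endpoint of its own. The same time points apply to the two composites.

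The abstract confirms the horizon: "Clinical follow-up for up to 5 years will be conducted by telephone". The planned size is 80 patients per group.

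**The concern.** A patient who dies of a cause outside the endpoint can no longer have the event. For device-oriented MACE, that cause is any non-cardiac death. For stent thrombosis, it is any death not due to thrombosis, which includes other cardiac deaths. These are competing events.

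Standard Kaplan-Meier knows only two statuses, event and censored. Used in the ordinary way, it censors these patients and treats them as exchangeable with survivors who remain at risk. The quantity 1 − KM then describes a hypothetical setting without other deaths and lies above the proportion of patients who actually have the event.

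What is at stake is the late absolute rates. The Background section motivates the trial by very late stent thrombosis and by a scaffold absorbed after about 2 years, so the 2- and 5-year device results matter to readers. Patient selection criteria set no upper age limit and admit acute coronary syndromes, so some deaths from other causes over 5 years are foreseeable. Patient-oriented rates would be actual risks and device-oriented rates would not, so the two composites would sit side by side on different scales.

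**Working it through.** The article gives no expected rate for any clinical endpoint, so there is no planned figure to reproduce. The check sizes the possible excess.

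**Inputs**

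- From the article: 80 patients per arm (Statistical analyses), and a MACE rate of 6.8% at 2 years in a cited scaffold study (Background). The latter serves only as an illustrative event rate.
- Assumed: 5-year probability of death outside the endpoint of 2, 5, 10 and 15%; constant hazards; alternative 5-year event rates of 15% and 30% for device-oriented MACE and 2% for stent thrombosis.

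**Formulas**, with h1 the event hazard, h2 the hazard of competing death, and T in years:

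- 1 − KM = 1 − exp(−h1·T)
- cumulative incidence = h1/(h1 + h2) × [1 − exp(−(h1 + h2)·T)]

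**Event hazard.** h1 = −ln(1 − 0.068)/2 = 0.0352 per year, so 1 − KM at 5 years = 1 − exp(−0.176) = 16.1%.

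**Worked case, 15% competing death.** h2 = −ln(0.85)/5 = 0.0325. Then h1/(h1 + h2) = 0.0352/0.0677 = 0.520, and 1 − exp(−0.3386) = 0.287. The cumulative incidence is 0.520 × 0.287 = 14.9%, so 1 − KM is 1.2 points too high.

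**Excess at 5 years**

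| Assumed competing death | 1 − KM 16.1%: true incidence (excess) | 1 − KM 15%: true incidence (excess) | Stent thrombosis, 1 − KM 2%: true incidence (excess) |
|---|---|---|---|
| 2% | 16.0% (0.16) | 14.85% (0.15) | 1.98% (0.02) |
| 5% | 15.7% (0.40) | 14.63% (0.37) | 1.95% (0.05) |
| 10% | 15.4% (0.80) | 14.26% (0.74) | 1.90% (0.10) |
| 15% | 14.9% (1.21) | 13.88% (1.12) | 1.85% (0.15) |

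Excess is in percentage points. For stent thrombosis, the first column stands for all deaths not due to thrombosis, so the lower rows are the more relevant ones.

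**Earlier times**, with the 6.8% input: the excess is 0.03 to 0.21 points at 2 years and 0.01 to 0.06 points at 1 year.

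**Upper stress case:** a 30% event rate with 15% competing death gives 27.8% against 30%, an excess of 2.2 points.

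**Against sampling error:** the standard error of a 15% rate in 80 patients is √(0.15 × 0.85/80) = 4.0 points. If one arm had 5% and another 15% competing death, the distortion of their difference at a 15% rate would be 1.12 − 0.37 = 0.75 points, against a standard error of the difference of √2 × 4.0 = 5.6 points.

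**The case against.** The strongest reply is that the article never says what the concern needs. It writes no censoring rule and does not state that 1 − KM will be reported as a 5-year risk. The same section says that categorical variables are given as counts and percentages. If that covers the endpoints, crude proportions would not carry this bias. A condensed article commonly leaves such rules to a full protocol or analysis plan, which is not shown. This stands in part. A reader might infer that the plan censors these deaths and therefore reports inflated rates, but the text supports only a conditional statement. What survives is that the article names one method for all endpoints, and that ordinary use of it censors these deaths unless a further rule is given.

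Second, the sentence is about comparison. A log-rank or Cox analysis that censors competing deaths is a valid comparison of cause-specific hazards. This stands in full. A reader might infer that the comparison of stents is invalid; it is not.

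Third, the hypothesis in Study objectives and hypothesis rests on late lumen loss at 9 months and on death, MI and TVR at 12 months. That composite counts all deaths and is unaffected. This also stands, and it confines the point to the device endpoints at late follow-up.

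Fourth, the effect is small beside the sampling error. This is true and limits the weight of the point. The bias is nevertheless always in one direction and would not shrink with more patients.

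**Conclusion.** The point holds as a minor improvement. If deaths outside the endpoint are censored and 1 − KM is reported as risk, the 5-year device-oriented rate would be about 0.2 to 1.2 points too high at a rate of 15 to 16%, and the stent thrombosis rate under about 0.2 points too high at 2%. At 12 months or earlier the excess is negligible. These sizes rest on constant hazards and on 2 to 15% competing death, which the article does not give. The 16% rate is itself an extrapolation from a cited 2-year figure whose MACE definition may differ from this trial's. Between-arm log-rank or Cox comparisons and the patient-oriented composite are not affected, and nothing here threatens the trial's main conclusions.

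**What to change.** In Statistical analyses, replace the single sentence on clinical endpoints with three statements:

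- Patient-oriented MACE is described by Kaplan-Meier.
- Device-oriented MACE and stent thrombosis are described by Aalen-Johansen cumulative incidence. The competing event is non-cardiac death for the former and any death not due to thrombosis for the latter.
- Arms are compared on these two endpoints by cause-specific log-rank test or Cox model.

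The cost is one additional standard routine and slightly lower stated rates. No new data are needed: the composite already requires cause of death, and the article has a Clinical Events Adjudication Committee that reviews all events. Sample size and trial conduct do not change.

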### Clinical follow-up

Patients will be followed clinically by clinic visits or by telephone interview at 3, 6, 9 and 12 months, and 2 and 5 years. No blinding will be present during the collection of outcome data. If the patient is not accessible, data can be retrieved from the referring physician or the hospital electronic database.

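### Predictors of MACE and stent thrombosis are sought with logistic regression, although the plan compares these endpoints by Kaplan-Meier; a Cox model would fit better where follow-up is incomplete (low priority)

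*Protocol article*

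**What the plan says.** The Statistical analyses section gives two methods for overlapping endpoints. For the comparison: "Clinical endpoints are compared using the Kaplan-Meier method". For the search for predictors: "Binary logistic regression is equally performed in the search of independent predictors for the secondary endpoints". It names no time-to-event regression.

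Under Study endpoints, the secondary endpoints are of two kinds:

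- Angiographic: "We will assess angiographic success, device success and binary restenosis at 9 months".
- Clinical: patient-oriented MACE, device-oriented MACE "and stent thrombosis (ST) at 6 months, and 1, 2 and 5 years".

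The Clinical follow-up section sets the schedule of contacts: "Patients will be followed clinically by clinic visits or by telephone interview at 3, 6, 9 and 12 months, and 2 and 5 years". For those who cannot be reached, it adds this provision: "If the patient is not accessible, data can be retrieved from the referring physician or the hospital electronic database".

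The article does not say at which of these time points the logistic model is fitted, or how a patient with incomplete follow-up enters it.

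**The concern.** Kaplan-Meier estimation credits each patient with the time observed and censors at last contact. Binary logistic regression needs a yes/no status for everyone. A patient lost before the chosen time point must therefore be dropped, or counted as event-free.

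Either choice can bias a predictor's coefficient when loss differs between levels of that predictor, and the two choices bias it in opposite directions. Such loss is plausible, because age and comorbidity are natural candidate predictors and there is no scheduled contact between 2 and 5 years. At stake is whether the predictors reported for MACE and stent thrombosis can be trusted, and whether they agree with the Kaplan-Meier curves printed beside them.

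**Working it through.** The plan gives no figure for the predictor analysis, so there is none to reproduce. The check asks how far logistic and Cox regression differ in a trial of this size.

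**Inputs from the article.** N = 240 in three groups of 80. Clinical follow-up runs to 5 years. The only MACE rate given is 6.8% at 2 years (Background, from an earlier study of the scaffold in 131 patients). At a constant hazard this extends to 1 − 0.932^2.5 = 16.1% at 5 years.

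**Assumptions.** One binary predictor with equal groups; 5-year event risk of 16%, 25% or 30%; exponential event times; and the loss rates shown below. The article gives no expected loss for clinical follow-up. Its 20% dropout allowance belongs to the 9-month late lumen loss sample size.

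**Step 1. Expected odds ratio when the predictor has no effect.** Let p be the 5-year event risk and L the proportion lost by 5 years. With constant rates, h = −ln(1 − p)/5 for events and c = −ln(1 − L)/5 for loss. Then:

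- observed event by 5 years: E = h/(h + c) × [1 − (1 − p)(1 − L)]
- known event-free at 5 years: S = (1 − p)(1 − L)
- odds if lost patients count as event-free: E/(1 − E)
- odds if lost patients are dropped: E/S

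For p = 16% and loss of 5% vs 40%, h = 0.0349 and c = 0.0103 vs 0.1022. This gives E = 0.156 vs 0.126 and S = 0.798 vs 0.504.

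- Counted event-free: (0.126/0.874) ÷ (0.156/0.844) = 0.78
- Dropped: (0.126/0.504) ÷ (0.156/0.798) = 1.28

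For p = 25% and loss of 20% vs 49% (1 − 0.8³), E = 0.225 vs 0.185 and S = 0.600 vs 0.384.

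- Counted event-free: (0.185/0.815) ÷ (0.225/0.775) = 0.78
- Dropped: (0.185/0.384) ÷ (0.225/0.600) = 1.28

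The true value is 1.00. With equal loss, E and S are the same in both groups and both odds ratios equal 1.00.

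**Step 2. False-positive rate at nominal 5%, by simulation with n = 240 and no true effect.**

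| 5-year loss by predictor level | Event risk | Logistic, lost counted event-free | Logistic, lost dropped | Cox |
|---|---|---|---|---|
| none, or 20% in both | 16% or 30% | 4.5-5.1% | not run | 4.4-4.7% |
| 5% vs 40% (exponential loss) | 16% | OR 0.78; 9.5% | OR 1.28; 9.5% | HR 1.00; 4.8% |
| 5% vs 40% (uniform loss times) | 16% | OR 0.80; 9.2% | not run | HR 1.00; 5.0% |
| 5% vs 40% (uniform loss times) | 30% | OR 0.80; 13.7% | not run | HR 1.02; 6.5% |
| 20% vs 49% | 25% | OR 0.78; 10.8% | OR 1.30; 11.6% | HR 1.01; 4.4% |

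The rows with uniform loss times and the no-loss or equal-loss row use 1,000 runs per scenario; the others use 4,000. With milder differential loss (10% vs 27%) and no effect, logistic rejection is only about 6-6.5%.

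**Step 3. Power with a true hazard ratio of 2 (lost counted event-free).** With no loss, power is the same: 70.5% logistic vs 70.2% Cox at a 16% event risk in the unexposed group. With loss of 5% vs 40%, it falls to 36% vs 66% at that risk, and 53% vs 90% at 30%.

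**The case against.** Much can be said for the plan as written.

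- **Some secondary endpoints suit logistic regression.** Binary restenosis, angiographic success and device success are yes/no outcomes at a fixed time. This stands, and the fix leaves them alone.
- **The model is not tied to 5 years.** MACE and stent thrombosis are reported at four time points, and the clinical hypothesis under Study objectives is placed at 12 months. At an early time point with status known for nearly all patients, a logistic model is ordinary practice. This stands. The figures above describe a 5-year model.
- **Loss is not documented, and data may be retrieved from physicians or hospital records.** Retrieval reduces loss but does not exclude it. The loss rates above are assumptions, and without differential loss the two methods barely differ.
- **An odds ratio is not a hazard ratio.** With a true hazard ratio of 2 and risks of 14.0% vs 26.0%, complete follow-up alone gives (0.260/0.740) ÷ (0.140/0.860) = 2.16. A gap between an odds ratio and a hazard ratio is therefore partly scale. For this reason the size of the bias is judged here on predictors with no effect, where both ratios should be 1.

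A reader might also infer that few events make the logistic search return spurious predictors. Ten null candidates at 5% do give 1 − 0.95^10 = 40% for at least one false finding. But ten is an assumed number, the same holds for Cox regression, and the number and selection of covariates are commonly left to the analysis plan. That is no ground for criticising this choice of model.

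**Conclusion.** The mismatch is real. The plan uses event time and censoring to compare MACE and stent thrombosis, then discards both when modelling the same endpoints.

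The harm is conditional. It arises only if loss to follow-up differs by predictor. Under strongly differential assumed loss, the false-positive rate is about twice the nominal 5% or somewhat more, and even the direction of the bias depends on a handling rule that the article does not give. Under complete or equal loss there is no practical difference. Cox regression corrects for loss that depends on predictors in the model; it would not correct loss that depends on outcome in other ways.

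A reader might infer that the estimated device effects are biased. The documents do not support that: the devices are compared on clinical endpoints by Kaplan-Meier, and nothing says a device effect will be taken from the logistic model. The primary late lumen loss analysis is separate. This is a low-priority improvement to an exploratory analysis.

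**What to change.** For patient-oriented MACE, device-oriented MACE and stent thrombosis, replace binary logistic regression with a Cox proportional-hazards model using the same event and censoring dates as the Kaplan-Meier curves. Report hazard ratios with 95% confidence intervals, labelled exploratory. Keep logistic regression for binary restenosis, angiographic success and device success.

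The cost is a change of wording. The event and last-contact dates are already needed for Kaplan-Meier, so no new data are required. The downside is that the proportional-hazards assumption must be checked.
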